## Abstract

Deqi, according to traditional Chinese medicine, is a specific needle sensation during the retention of needles at certain acupoints and is considered to be necessary to produce therapeutic effects from acupuncture. Although some modern researches have showed that Deqi is essential for producing acupuncture analgesia and anesthesia, the data are not enough. It is a paper of a multicenter, randomized controlled study protocol, to evaluate the influences of Deqi on acupuncture SP6 in Cold and Dampness Stagnation pattern primary dysmenorrhea patients, in terms of reducing pain and anxiety, and to find out the relationship between Deqi and the temperature changes at SP6 (Sanyinjiao) and CV4 (Guanyuan). The results of this trial will be helpful to explain the role of Deqi in acupuncture analgesia and may provide a new objective index for measuring Deqi in the future study. This trial is registered with ChiCTR-TRC-13003086.

## 1. Introduction

Deqi, according to records in both ancient and modern books of traditional Chinese medicine (TCM), is a specific needle sensation which usually occurs during retention of acupuncture needles at certain acupoints, and both patients and acupuncturists can feel the Deqi sensation. It is regarded as a necessary factor for producing effects from acupuncture following traditional Chinese medicine theory. Patients can feel Deqi as multiple sensations at the needling acupoints and along the meridians sometime, such as soreness, numbness, distension, or a minimal muscular contraction around the needle [1–3] and also objective physiological changes, such as the skin temperature changes at the acupoints [4] or the response of brain [5, 6]. For acupuncturists, they can feel a change of the mechanical behavior of the tissues surrounding the needle, such as an increase of the force necessary to pull the needle out of the tissue (pullout force) [7]. Although some modern research showed that Deqi is essential for producing acupuncture analgesia and anesthesia [8], new evidence to confirm the conclusion is still urgently needed [9, 10].

Primary dysmenorrhea (PD) refers to painful menstrual cramps without any evident pathology. It is characterized by crampy suprapubic pain with radiation into the lower quadrants, the lumbar area, and the thighs [11]. PD is a common gynecological complaint and significantly affects study, work, sports, and social activities [12–18]. So far nonsteroidal anti-inflammatory drugs (NSAIDs) or oral contraceptive pills (OCPs) are widely advocated as standard treatments for women with PD [19, 20]. However, acupuncture as nonpharmacological approaches has great potential value.

Acupuncture is one of the main treatment modalities of TCM. Several trials [21, 22] have already demonstrated the encouraging results of acupuncture as a nonpharmacological option for the treatment of PD. Two systematic reviews also demonstrated the effect [23] and cost-effectiveness [24] of this therapy. The acupoint SP6 (Sanyinjiao) is found to be one of the most commonly used points encountered when searching ancient Chinese medical classics, Chinese acupuncture textbooks, and clinical trials using acupuncture-related therapies for PD [25, 26]. Previous randomized controlled trials have showed that acupuncture at SP6 (Sanyinjiao) can relieve the pain of PD immediately [27–29] especially for PD patients with Cold and Dampness Stagnation pattern [30], which is the most common pattern in PD patients [31, 32]. Langevin's study [7] also showed that, compared with the nonacupoint control group, the average pullout force in SP6 (Sanyinjiao) was greater, which suggested that SP6 (Sanyinjiao) might be especially sensitive in Deqi.

In this study, we will perform a randomized controlled trial using SP6 to investigate the influences of Deqi on immediate analgesia effects in PD patients with Cold and Dampness Stagnation pattern. The primary objective of this trial is to evaluate the influences of Deqi on acupuncture therapy, in terms of pain reduction (measured on a 0–100 mm visual analogue scale for pain (VAS-P)) achieved before and after intervention (i.e., before and after 30 minutes of treatment). The secondary objectives are as follows: (1) to evaluate the influences of anxiety reduction on a 0–100 mm visual analogue scale for anxiety (VAS-A) and (2) to evaluate the influences of temperature changes at SP6 (Sanyinjiao) and CV4 (Guanyuan) acupoints monitor by a digital infrared thermographic imaging device (only in the Dongzhimen Hospital).

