### 2.4. Interventions

All participants, when their VAS-P score of menstrual pain is equal to or more than 40 mm on the first day of menstruation, will each receive an acupuncture treatment for 30 minutes at bilateral SP6 acupoints. The SP6 lies on the tibial aspect of the leg, is posterior to the medial border of the tibia, and is 3 B-cun (proportional bone cun) superior to the prominence of the medial malleolus [35].

*(a) Deqi Group*. The treatment will be performed after sterilizing the skin on the areas where the needles will be inserted, with participants lying face up. Using single-use sterile needles (Zhongyan Taihe, Wuxi Jiajian Medical Instrument Co. Ltd., Jiangsu, China) of 0.30 mm calibre and 40 mm length, a needle will be vertically inserted 1 cun in depth and will be manipulated by lifting-thrusting and twirling methods for 30 seconds to achieve Deqi.

*(b) No Deqi Group*. Single-use sterile needles (Zhongyan Taihe, Wuxi Jiajian Medical Instrument Co. Ltd., Jiangsu, China) of 0.18 mm calibre and 13 mm length will be used. The treatment will be performed after sterilizing the skin on the areas where the needles will be inserted, with participants lying face up. A needle will be vertically inserted 0.1 cun in depth. No manipulation will be performed after insertion of needles to avoid Deqi.

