## 3. Discussion

The trial is designed to illustrate Deqi effect on acupuncture treatment. It will estimate Deqi state of solo acupoint and compare analgesic right after needling. All participants will be randomly divided into Deqi or no Deqi group. Unlike other impact factors of acupuncture treatment, Deqi is a group of specific subjective sensations which can only be felt during acupuncture by both patients and acupuncturists. It is impossible to randomly allocate participants into a Deqi or no Deqi group, so there have been no Deqi randomized controlled trials (RCTs). However, whether Deqi can be achieved during acupuncture can be predicted to a certain extent; therefore, we will randomly divide all participants into Deqi or no Deqi group. We also employ manipulation technique to promote Deqi in the Deqi group, while in the no Deqi group we avoid Deqi according to TCM theory and experts' experience.

In this study, we will use an important self-designed instrument—Acupuncture Deqi Clinical Assessment Scale (ADCAS). The scale shows the intensity of participants' sensation, ranging from 0 to 4: 0 (no), 1 (slight), 2 (mild), 3 (obvious), and 4 (strong). It will be firstly used as an instrument for redividing all the included participants in reanalysis. Actually, some researchers and their colleagues have attempted to qualify and quantify sensations of Deqi [41–47] and designed several Deqi scales or questionnaires like the Vincent scale, the Park questionnaire, the MGH Acupuncture Sensation Scale (MASS), and Southampton Needling Sensation Questionnaire (SNSQ). Some of the scales or questionnaires have been used in Deqi trials [48–50] and MASS even has a Chinese edition [51]. However, though Deqi sensation can be felt by patients and acupuncturists, all the current scales take no consideration of the Deqi sensation felt by acupuncturists' hands, which decreases the reliability of those scales.

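### The objective concerns Deqi itself, but the randomised contrast is between two needling regimens, and the planned regrouping by Deqi score does not separate them

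*Protocol article*

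**What the plan says.** **Target of inference.** The Introduction says "The primary objective of this trial is to evaluate the influences of Deqi on acupuncture therapy, in terms of pain reduction". The Abstract and the end of the Discussion expect the results to help explain what Deqi contributes to acupuncture analgesia. The Abstract and Introduction define Deqi as a needle sensation; the Introduction adds that the acupuncturist can feel a change in the tissue.

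**What is allocated (section 2.4).** Both arms receive 30 minutes at bilateral SP6, lying face up. In the Deqi group the needle is "of 0.30 mm calibre and 40 mm length" and "a needle will be vertically inserted 1 cun in depth and will be manipulated by lifting-thrusting and twirling methods for 30 seconds to achieve Deqi". In the No Deqi group needles "of 0.18 mm calibre and 13 mm length will be used". "A needle will be vertically inserted 0.1 cun in depth", and "No manipulation will be performed after insertion of needles to avoid Deqi".

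**What the authors concede.** The Discussion says "It is impossible to randomly allocate participants into a Deqi or no Deqi group". It then explains that achieving Deqi can be partly predicted, so patients are randomised to groups in which it is promoted or avoided. Section 2.8 accepts that some Deqi-group patients will probably not feel it.

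**The planned response (section 2.8).** After treatment all participants are re-sorted by ADCAS grade into real and unreal Deqi groups. They are then analysed with a method similar to the primary one, and the two sets of results are compared. Table 1 has ADCAS collected at T1.

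**The concern.** The quantity named in the objective is not the quantity that randomisation identifies. Depth, calibre and manipulation are fixed by arm, and each could affect pain whether or not the patient feels Deqi. If VAS-P falls more in the Deqi group, the primary comparison shows that the regimen worked better but does not show that the sensation was the reason. If there is no difference, Deqi is not thereby shown to be irrelevant, because arm and Deqi do not coincide fully.

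The ADCAS regrouping is the only analysis aimed at Deqi as experienced. Its groups form after randomisation and remain tied to arm, because one regimen is designed to produce Deqi and the other to prevent it. If both analyses point the same way, readers will take the second as confirming the first, although the same regimen difference may drive both.

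**Working it through.** This is a question of identification, so there is no stated figure to correct. The plan's only derived number is 48 per group, which is 40 × 1.20 (section 2.2.1). The point does not depend on it.

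**Step 1: what differs by arm (section 2.4).**

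| Feature | Deqi group | No Deqi group | Ratio |
|---|---|---|---|
| Calibre | 0.30 mm | 0.18 mm | 0.30/0.18 = 1.67 |
| Depth | 1 cun | 0.1 cun | 1/0.1 = 10 |
| Manipulation | 30 s | none | – |

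Needle length (40 vs 13 mm) goes with depth and is not counted separately. No arm holds these features constant while Deqi varies, so the primary contrast returns their joint effect plus any effect of Deqi. These ratios describe the needling; they do not measure bias in VAS-P.

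**Step 2: primary test when Deqi has no effect.** The assumptions are not from the document: regimen effect 10 mm, Deqi effect 0, two-sided alpha 0.05. I take 40 per arm, the plan's base number. Normal approximation: power = Φ(10 / (SD × √(2/40)) − 1.96).

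- SD 15 mm: 10/3.354 = 2.98, power 0.85
- SD 20 mm: 10/4.472 = 2.24, power 0.61
- SD 25 mm: 10/5.590 = 1.79, power 0.43

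A significant result would be quite likely although Deqi contributes nothing.

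**Step 3: regrouped analysis under the same assumptions.** Let pA and pB be the proportions feeling Deqi in the Deqi and No Deqi arms, with equal arms and feeling Deqi unrelated to pain within arm. The share from the Deqi arm is pA/(pA+pB) among those who feel Deqi and (1−pA)/((1−pA)+(1−pB)) among those who do not. The apparent Deqi effect is 10 mm times the difference in shares.

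| pA / pB | Share, felt | Share, not felt | Apparent effect |
|---|---|---|---|
| 90% / 10% | 0.90 | 0.10 | 8.0 mm |
| 80% / 20% | 0.80 | 0.20 | 6.0 mm |
| 70% / 30% | 0.70 | 0.30 | 4.0 mm |
| 60% / 40% | 0.60 | 0.40 | 2.0 mm |

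The true Deqi effect is zero in every row. The artefact vanishes only if Deqi is equally common in both arms, in which case the regimens have failed to separate Deqi.

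**Step 4: what comparing within arm costs.** At 90%/10% with 40 per arm, each arm splits 36 to 4. The standard error of the within-arm difference, averaged over two arms, is SD × √(1/36 + 1/4)/√2 = 0.373 SD. The pooled 40 vs 40 split has SD × √(2/40) = 0.224 SD, so the standard error is 1.67 times as large. At 70%/30% (28 to 12) it is SD × √(1/28 + 1/12)/√2 = 0.244 SD, or 1.09 times. Precision therefore falls as the regimens succeed in separating Deqi. This ignores any fall in residual SD from removing the arm difference.

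**The case against.** The strongest reply is that the authors know this. A reader might infer from the Discussion that the protocol contradicts itself by calling random allocation to Deqi impossible and then randomising to Deqi groups. The text does not support that: the next sentences explain that Deqi can be partly predicted and is promoted in one arm and avoided in the other. That is an openly described encouragement-type design. Nor was imperfect correspondence between arm and Deqi overlooked; the section 2.8 re-analysis is aimed at it.

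Some bundling is also unavoidable. Manipulation is the means of obtaining Deqi, and the Introduction's account of Deqi includes tissue changes felt by the acupuncturist. This defends the manipulation difference better than the calibre difference.

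Two further readings go too far. A reader might infer that a positive result would be explained just as well by stimulation without Deqi, but nothing in the document gives the relative contributions; it can only be said that they are not separable. A reader might also infer that the trial is invalid. It is not: allocation, outcome and primary test stand as a comparison of regimens. Finally, this is a protocol with hedged expectations and no reported conclusion, and the figures in steps 2 and 3 of the working rest on assumed effects, SDs and Deqi rates.

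All of that stands and limits the point without removing it. The objective is still worded as the effect of Deqi, and an encouragement design isolates Deqi only if arm acts on pain solely through Deqi, which the other needling differences make doubtful. The one analysis offered as a remedy is described without any term for arm.

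**Conclusion.** The point holds as a mismatch between objective and contrast. The randomised comparison validly estimates the immediate effect on VAS-P of a Deqi-seeking versus a Deqi-avoiding regimen, and it cannot separate Deqi from calibre, depth and manipulation. The ADCAS regrouping as described does not repair this, because a pure regimen effect appears as a Deqi effect whenever Deqi is commoner in the Deqi arm.

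The size of the problem in this trial cannot be known from the document, which gives no effect size, SD or expected Deqi rates. On an assumed 10 mm regimen effect and no Deqi effect, the regrouped analysis would show 2 to 8 mm across the rates in the table. The qualitative conclusion needs only that the regimen can affect pain by some route other than Deqi and that Deqi is commoner in the Deqi arm. The second is what the design intends.

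**What to change.** 1. Restate the primary objective and intended conclusion, in the Abstract, Introduction and Discussion, as the immediate effect on VAS-P of a needling regimen intended to elicit Deqi compared with one intended to avoid it.
2. Report the ADCAS distribution by arm as a manipulation check, using the T1 data already planned.
3. Replace the pooled regrouping with an ADCAS analysis done within arm or with a term for arm. Label it non-randomised and exploratory, and confine statements about Deqi itself to it. State that patient characteristics may still confound it and that it will be imprecise if few patients are discordant with their arm.

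The cost is rewording, one table and one model term, with no new data. The headline claim becomes narrower and the secondary analysis less precise. No change to the needling is proposed.

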## 2. Methods

### 2.1. Ethics

The trial protocol is in accordance with the principle of the Declaration of Helsinki [33] and has been approved by the Ethic Committee of Beijing University of Chinese Medicine (Beijing, China, Approval number 2012-040). Each participant will be notified regarding the study protocol. Written informed consent will be obtained from each participant.

### 2.2. Settings and Participants

A target sample of 96 participants will be recruited in acupuncture clinic from the following four hospitals: Dongzhimen Hospital Affiliated to Beijing University of Chinese Medicine, Beijing Hospital of Traditional Chinese Medicine affiliated to Capital Medical University, Huguosi Hospital of Traditional Chinese Medicine affiliated to Beijing University of Chinese Medicine, and Hebei Medical University. The trial will be conducted from March 2013 to March 2015.

#### 2.2.1. Sample Size

This is a study without similar references as we know and 40 patients per group is acceptable for calculating sample size for further studies. Assuming a dropout rate of 20%, we will plan to enroll a total of 96 participants with 48 in each group.

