### 2.3. Randomization and Blinding

The central randomization will be performed by the Center for Evidence-Based Chinese Medicine affiliated to Beijing University of Chinese Medicine in China, using complete randomization to generate the random allocation sequence. Once a participant is included, the researcher will contact the randomization center for the group allocation of the participant, and the acupuncturist will be informed by telephone. Participants will be allocated at a 1 : 1 ratio (Figure 1).

The participants will be informed that they will have a 50% chance of being allocated in either of the two acupuncture groups, and both groups will be potentially effective; hence, participants will be blinded to the group allocation. The patients will also be informed of the possible risks associated with acupuncture (hematoma or fainting). The acupuncturist cannot be blinded due to the specific nature of intervention. Outcome assessors and personnel who will deal with data collection and data analysis will be blinded throughout the entire trial.

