### 2.5. Outcome Measures

#### 2.5.1. Primary Outcome Measures

The changes of pain will be measured by visual analogue scale for pain (VAS-P), before and after the treatment. The validity and reliability of the VAS-P scale have been proven [36–38] and it was employed in our previous similar studies [29, 30]. The scale measures a continuous quantitative variable varying from 0 mm (no pain) to 100 mm (worst pain ever).

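### The 20% dropout allowance is added as 40 × 1.2 = 48 per group, but 20% dropout from 48 leaves about 38, not 40: a small arithmetic slip

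*Protocol article*

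**What the plan says.** The sample size rationale is in section 2.2.1 of the protocol article and has three elements.

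- **Starting number.** The authors know of no similar study to draw on and take a pragmatic figure: "40 patients per group is acceptable for calculating sample size for further studies".
- **Dropout and enrolment.** The allowance and the resulting enrolment follow in the next sentence: "Assuming a dropout rate of 20%, we will plan to enroll a total of 96 participants with 48 in each group".
- **Repetition.** Section 2.2 gives the same total: "A target sample of 96 participants will be recruited". Section 2.3 sets the allocation: "Participants will be allocated at a 1 : 1 ratio".

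The article gives no effect size, standard deviation or power for the 40. It gives no other dropout rate and no other reason for 48 per group.

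**The concern.** Both inputs (40 per group, 20% dropout) and the output (48 per group, 96 in total) stand side by side, so a reader can check the step directly, and it does not work. A dropout rate is conventionally the fraction of enrolled participants who are lost. To keep *n* after losing a fraction *d*, one enrols *n* / (1 − *d*). The article's figure is *n* × (1 + *d*), which takes the percentage of the number to be kept instead of the number enrolled. This always gives too few.

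What is at stake is limited. If dropout runs at the assumed rate, the trial should expect to finish slightly below the number it was sized on. The step also deserves to be right because 40 and 20% are the whole of the published rationale, and because the article presents the 40 as a basis for sizing later studies, where the same inflation could be copied.

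**Working it through.** **Inputs**

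- Number to remain per group: *n* = 40 (section 2.2.1). The article does not say in words that this is the number after dropout. That is the natural reading, since the allowance is added on top of it.
- Dropout rate: *d* = 0.20 (section 2.2.1).
- Planned enrolment: 48 per group, 96 in total (section 2.2.1; the total is repeated in section 2.2).
- Allocation: 1 : 1 (section 2.3).

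**Step 1. Reproduce the article's figure.**
*n* × (1 + *d*) = 40 × 1.20 = 48 per group; 2 × 48 = 96. This matches exactly.

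**Step 2. Apply the stated dropout to the stated enrolment.**
48 × (1 − 0.20) = 38.4 per group; 96 × 0.80 = 76.8 in total.
Against the target of 40 per group (80 in total), the expected shortfall is 40 − 38.4 = 1.6 per group and 80 − 76.8 = 3.2 in total.

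**Step 3. Enrolment that follows from the inputs.**
*n* / (1 − *d*) = 40 / 0.80 = 50 per group; 2 × 50 = 100 in total, which is 4 more than stated.

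**Step 4. Dropout rate that 48 per group can absorb.**
1 − 40/48 = 8/48 = 16.7%.

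**Step 5. What this means in practice.** Assume that dropouts are independent, each with probability 0.20, and that the groups have exactly the planned size.

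| Enrolled per group | Chance that one group keeps at least 40 | Chance that both do |
|---|---|---|
| 48 | 0.358 | 0.358² = 0.128 |
| 50 | 0.584 | 0.584² = 0.341 |

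Even 50 per group meets the target only on average, so it is no guarantee.

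**Step 6. Effect on precision.** The approximate half-width of a 95% confidence interval for a between-group difference, in SD units, is 1.96 × √(2/*n*):

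- *n* = 40: 1.96 × √(2/40) = 0.438 SD
- *n* = 38.4: 1.96 × √(2/38.4) = 0.447 SD

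The interval widens by 0.009 SD, about 2% of its half-width (0.009 / 0.438).

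**The case against.** **The article never says that 40 is the number after dropout.** This is true, and the point should not attribute a word such as evaluable to it. But if 40 were the enrolment figure, there would be no reason to add an allowance and enrol 48. The 40 makes sense only as the number meant to remain.

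**The 20% may be meant as a simple uplift on 40.** In that case 48 is what was intended, but the description is wrong: 8 extra patients among 48 enrolled cover a dropout rate of 16.7%, not 20%. The sentence needs the same correction.

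**The effect is trivial.** Largely conceded. The gap is 1.6 patients per group and precision hardly changes. If the randomization is unrestricted, as section 2.3 may mean, the size of one group among 96 varies with an SD of √96 / 2 = 4.9, about three times the shortfall. So 100 should not be presented as the number that secures 40 per group. The target of 96 is consistent between sections 2.2 and 2.2.1 and can be carried out as written. What fails is the link from 40 and 20% to 48.

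**Stronger readings that the article does not support**

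- *The trial is underpowered.* The article claims no power, effect size or SD, and offers 40 as a pragmatic number. No stated power is lost, and a request for a detectable difference would be a separate wish for more detail.
- *The article contradicts itself about having no similar studies to draw on.* A reader might infer this from section 2.5.1, which says of the pain scale that "it was employed in our previous similar studies". The two statements are compatible. The Discussion explains that randomized trials of Deqi itself have not been done, while earlier studies can have used the same scale for other comparisons.
- *A usable SD for VAS-P is therefore at hand.* Section 2.5.1 gives no SD. Whether the cited studies report one, and for the before-to-after change that is the outcome here, cannot be known from this document.

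**Conclusion.** The point holds as a minor arithmetic error. The enrolment of 48 per group (96 in total) results from multiplying 40 by 1.2. At the stated 20% dropout it leaves about 38 per group, and it reaches 40 only if dropout is at most 16.7%. The stated inputs lead to 50 per group, 100 in total.

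This rests on two assumptions: that 40 is the number meant to remain after dropout, and that the dropout rate is a share of those enrolled. Both are the ordinary reading, and nothing else in the article points elsewhere. The finding concerns whether the published rationale is correct. It does not show that the trial is too small for its purpose, and the design and analysis need not change because of it.

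**What to change.** Keep 96 and correct the sentence in section 2.2.1, for example:

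> We will enrol 96 participants, 48 per group. With 20% dropout this leaves about 38 per group; it leaves 40 per group if dropout is at most 16.7%.

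Section 2.2 then needs no change. The cost is one sentence and a slightly less favourable number of expected completers, with no extra patients.

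The alternative is to keep both 40 per group and 20% dropout and enrol 50 per group, 100 in total. That costs 4 more participants, and sections 2.2 and 2.2.1 would have to change together. Given the size of the gap, restating the figure is sufficient.
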